### Statistical analysis methods

The data obtained will be analyzed using SPSS Statistics version 18 (IBM Corp) software and evaluated using comparative and descriptive statistics. Student *t*-test will be used for normally distributed parametric data, while Mann-Whitney U-test will be used for non-normally distributed data. The χ^2^ test and Fisher exact test will be used to evaluate categorical data. A correlation between data will be evaluated using Pearson correlation coefficients for parametric data and Spearman correlation coefficients for non-parametric data. Descriptive statistics will be presented as median (range), mean ± SD, or number/frequency (percentage). Statistics will be considered significant when the *P*-value < 0.05.

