#### Model-building procedures (including predictor selection)

After the data set is imported into the R software, it will be divided into 80% training data and 20% validation data. The training data will be used to build the warning model, and the validation data will be used for internal validation.

To begin with, we will use R software to read the features of the dataset. After that, we will load the two R packages “corrplot” and “glmnet.” By using the cor() function, we will create a correlation object “corrlate” and visualize the correlation coefficient. The predictors and outcome variables in the training and validation sets will be encoded into matrices, the predictors will be stored in X vectors, and the outcome variables in Y vectors. A LASSO regression will be performed when alpha is set to one. The program will then be run. When the parameter lambda is greater, the estimated parameters will also be compressed to a smaller degree. As lambda reaches a certain value, some variables that are not important to the model will be compressed to zero, indicating that these variables will be eliminated. Thus, the lambda corresponding to the optimal result, the influencing factors of preliminary screening, and the regression coefficient will be obtained.

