#### Internal validation and assessment of model performance

Internal validation will be conducted using the 20% validation set samples and will utilize a cross-validation method based on 10 folds. Then, the result of LASSO cross-validation will be obtained, and the lambda when it is one standard error away from the mean square error will be considered optimal (at this time, the mean square error is small, and the number of independent variables is also small). For that lambda case, we will examine the regression coefficients and exclude variables with a regression coefficient of zero. Those variables with regression coefficients other than zero are selected, thereby identifying the influencing factors that are significantly associated with depression in PCOS adolescents. After screening the variables, a multivariate linear model will be constructed.

The prediction accuracy of the model will be reflected by discrimination and calibration. In this study, the C-statistic is used to measure discrimination, followed by a calibration plot to measure the accuracy of the absolute risk predictions of the warning model. An evaluation of the fit will be performed by drawing a scatter plot.

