## Discussion

This research protocol aims to construct and validate a warning model for depression in adolescents with PCOS. It will answer three questions: what factors influence depression risk in adolescents with PCOS; what role do various types of depression risk factors play in the development of depression in adolescents with PCOS; and how interpretable and accurate is the LASSO-based warning system.

There are many factors associated with depression in adolescents with PCOS. For the first time, a depression warning model will be constructed that takes into account not only general factors like individual susceptibility factors, biological factors, and psychosocial environmental factors of depression in adolescence, but also the pathological factors, illness perception factors, diagnosis and treatment factors, and symptom-related factors of PCOS. This study will precisely and early identify depression at-risk groups for PCOS in adolescence by including the influencing factors of several dimensions of depression into the model and leveraging LASSO's ability to automatically screen variables and boost model interpretability.

So far, it has been difficult to identify adolescents at high-risk of depression, which has a severe impact on adolescent mental health. In this study, the research population consists of adolescents with PCOS, who have a significantly greater prevalence of depression and more complicated impacts than general adolescent girls, an important representative sample. Through this study, we hope to remove the bottleneck of identifying adolescents at risk of depression. The success of this study can not only identify the high-risk groups of depression in adolescents with PCOS, but also demonstrate the risk factors and key links associated with depression in adolescents with PCOS. At the same time, it can be extended and applied to the management of high-risk groups of depression throughout adolescent girls, thereby contributing to reducing the prevalence of depression in adolescent girls and implementing comprehensive and effective prevention measures.

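### Non-zero LASSO coefficients are labelled as significant associations, although selection tests nothing and does not meet the protocol's own P < 0.05 criterion

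*Protocol article*

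**What the plan says.** Under Model-building procedures the protocol article states: "A LASSO regression will be performed when alpha is set to one". Here alpha is the glmnet mixing parameter, not a type I error rate. Under Internal validation and assessment of model performance it fixes the penalty: "the lambda when it is one standard error away from the mean square error will be considered optimal". The rule at issue follows: every variable whose coefficient is not zero is kept, "thereby identifying the influencing factors that are significantly associated with depression in PCOS adolescents". A multivariable model on the retained variables comes after that sentence. No test, interval, stability check or error control is attached to the claim of significance.

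Two other places bear on it. Statistical analysis methods defines significance: "Statistics will be considered significant when the *P*-value < 0.05". The Discussion lists three questions the study will answer, the first being "what factors influence depression risk in adolescents with PCOS".

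On the data used, "it will be divided into 80% training data and 20% validation data", and then "Internal validation will be conducted using the 20% validation set samples and will utilize a cross-validation method based on 10 folds". The second sentence leaves open whether lambda is tuned on the training part or on the 20% part.

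**The concern.** The quoted rule makes selection itself the ground for significance. A LASSO coefficient is non-zero because keeping the variable helped at a penalty chosen for prediction error. That is a reasonable way to choose predictors, but it says nothing about the chance that a variable with no effect is kept. The article thus uses two incompatible meanings of significance: P below 0.05 in one section, and not shrunk to zero in another.

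Table 1 makes this more than a matter of terms. Several candidates overlap: BMI with waist-to-hip ratio; total testosterone with sex hormone-binding globulin and the free testosterone index; duration of illness with duration of medication. Among such variables LASSO may keep one and drop another for reasons unrelated to the strength of evidence. At stake is a published list of risk factors carrying a label that the method cannot supply.

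**Working it through.** **1. The plan's own figure.** n = (1.96/δ)² × φ(1 − φ) = (1.96/0.05)² × 0.4 × 0.6 = 368.79, rounded up to 369. The stated minimum is reproduced. It concerns only the precision of the overall proportion and lends no support to the selection or significance of individual predictors.

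**2. Sample available for selection.** The article expects 800 patients with PCOS over January to December 2022, with January to August used for development. Assuming even accrual:
- development: 800 × 8/12 ≈ 533
- training: 533 × 0.8 ≈ 427
- internal validation: 533 × 0.2 ≈ 107

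**3. Number of candidates.** Table 1 has 31 rows (11 + 2 + 1 + 2 + 3 + 1 + 11). Dummy coding adds parameters; 45 is taken as an assumed larger value.

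**4. Simulation with 31 predictors.** LASSO with squared-error loss on a 0/1 outcome, prevalence 0.4, standardised predictors, 10-fold cross-validation on mean square error, one-standard-error lambda, 200 replicates per setting. The article gives no effect sizes or correlations, so these are assumed: log-odds 0.4 or 0.7 per SD, and common correlation ρ of 0 or 0.3. A noise variable is one with no conditional effect.

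Results at n = 427:

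| Real effects | Log-odds | ρ | Real kept | Noise kept | Runs with ≥ 1 noise | Noise share |
|---|---|---|---|---|---|---|
| 5 | 0.4 | 0 | 4.6 | 1.31 | 0.61 | 22% |
| 5 | 0.4 | 0.3 | 4.8 | 2.59 | 0.90 | 35% |
| 8 | 0.4 | 0 | 7.6 | 2.46 | 0.84 | 24% |
| 8 | 0.4 | 0.3 | 7.6 | 3.94 | 0.99 | 34% |
| 5 | 0.7 | 0 | 5.0 | 1.06 | 0.56 | 18% |
| 5 | 0.7 | 0.3 | 5.0 | 2.38 | 0.88 | 32% |
| 0 | – | 0 / 0.3 | – | 0.07 / 0.06 | 0.03 / 0.04 | – |

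**5. Simulation with 45 parameters.** Eight real effects, n = 427, the same lambda rule, 120 replicates. At a true C-statistic of 0.67, 2.75 of 6.03 retained variables were noise (46%), with at least one in 79% of runs. At 0.79, 4.58 of 11.55 were noise (40%), with at least one in 99%. The coefficients and correlations behind these runs are not set out here, so they serve only as the upper end of the range.

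**6. If lambda is tuned on the 20% part.** At n = 107, 31 predictors, log-odds 0.4 and 5 or 8 real effects, the noise share was 37–49%, with at least one noise variable in 30–93% of runs. Under a complete null, 9–12% of runs selected something.

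**The case against.** The strongest reply is that this is loose wording in a prediction study. The stated objectives are to develop and validate a model, and none is inference on single factors. The model-building section describes the same output as a preliminary screen, and the one-standard-error rule is deliberately sparse. All of this is correct, and it limits the point: discrimination, calibration and the nomogram do not depend on the phrase. It does not rescue the sentence, because the later section turns the screen into a statement of significance and the Discussion poses the explanatory question outright.

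Three stronger readings are tempting, and the article does not support them.
- *LASSO is the only planned answer to the Discussion's first question.* Statistical analysis methods also plans two-group tests and correlations at P below 0.05. They are not tied to that question, but they are there.
- *Invalid P-values will be reported from the refitted model.* None are announced; the model is to be judged on discrimination and calibration.
- *Noise variables will certainly be reported as established factors.* The rates depend on assumed effects and correlations, and with no true predictor the rule nearly always selects nothing. With ρ = 0.3, a variable without an independent effect still has a marginal association, so calling it associated need not be false. With ρ = 0 there is no association of either kind, and the noise share was still 18–24%.

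The sample is also open to question. The clinic's 80–100 patients a month would give 80 × 8 × 0.8 = 512 to 100 × 8 × 0.8 = 640 for training before exclusions. Those sizes were not simulated.

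**Conclusion.** The point stands as an error in what is written, not as missing detail. A non-zero penalised coefficient is not a significant association, and the rule contradicts the article's own definition of significance. The mislabelling would carry into the answer to the Discussion's first question.

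If some predictors truly matter, variables with no independent effect are likely, though not certain, to be among those selected: roughly 18–46% of them, with at least one in 56–99% of runs. This rests on even accrual (training n about 427), 31 to 45 candidate parameters, 5 to 8 real effects, and the assumed effect sizes and correlations. Under a complete null the figure is only about 3–4% of runs with any selection. The article should change the sentence; the prediction aim survives intact.

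**What to change.** Replace the claim of significance in the internal-validation section with: *variables with non-zero coefficients are selected as predictors; selection is not evidence of a statistically significant association*. Report each candidate's selection frequency over bootstrap repeats (for example 500) of the whole selection procedure, including the tuning of lambda. Answer the Discussion's first question in terms of selected predictors and how stably they are selected.

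The cost is a change of wording and some computing. The downside is that fewer factors can be claimed. No data collection changes.

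A single logistic model holding all candidates is not recommended as a substitute. With 45 parameters and about 427 × 0.4 ≈ 171 training events, it has about 3.8 events per parameter. With 45 − 8 = 37 null parameters tested at 0.05 and no multiplicity control, it would yield about 37 × 0.05 = 1.85 false positives, and at least one with probability 1 − 0.95³⁷ ≈ 0.85 if the tests were independent. It would also meet the collinearity that the Introduction gives as a reason for using LASSO.

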
**Figure 1 F1:**
[figure not shown]
Simulation map of risk factors for depression in adolescents with PCOS.

As previously noted, the occurrence of depression in adolescents with PCOS involves multiple dimensions and contains numerous independent variables. To minimize the bias caused by the absence of important independent variables, it's important to select as many variables as possible at the beginning of the warning model construction process. Traditional regression analysis methods using statistical software such as SPSS, Jamovi, etc., can quantitatively analyze the strength of a predictor based on the regression coefficient. However, conventional regression analysis methods cannot handle collinearity problems and produce high variance when there are numerous independent variables. Least Absolute Shrinkage and Selection Operator (LASSO) is a type of machine learning method introduced by Tibshiran in 1996 (26). On the one hand, LASSO can select features automatically. When there are numerous independent variables, LASSO can selectively integrate powerful explanatory factors into the model. On the other hand, LASSO can compress the coefficients of some minor or insignificant independent variables to zero and pick more relevant independent variables to prevent overfitting. As compared to traditional regression analysis methods, LASSO can process all independent variables simultaneously, which greatly increases the model's stability. LASSO has been gradually applied to the development of warning models in the medical area in recent years (27, 28), as it offers high stability, fast calculation speed, and ease of interpretation in building warning models. To date, LASSO has been applied to the construction of diagnostic prediction models, early risk identification of ischemic stroke, for example (27). LASSO has also been applied to the construction of prognostic prediction models, for instance, survival after ampullary adenocarcinoma resection (28). Additionally, a study based on LASSO used electronic primary care data to develop a predictive model of common mental disorders among adolescents and early adults (29). But the study noted that primary care data underestimated common mental disorders. Due to race and PCOS, the model cannot predict depression with PCOS in adolescents. Thus, we will explore the causes of depression in teenagers with PCOS and the influence of a variety of risk variables, as well as develop and test a depression risk prediction model for adolescents with PCOS. Not only will this model be able to identify high-risk groups for depression with PCOS in adolescence, but also for high-risk groups of depression in general adolescent girls.

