### Sample size and calculation

In the case of a binary outcome, an approximate 95% confidence interval for the total outcome proportion (ϕ) is

$$\begin{array}{l} \hat{\phi }\pm 1.96\sqrt{\frac{\hat{\phi }\left(1-\hat{\phi }\right)}{n}}, \end{array}$$

Therefore, the absolute margin of error (δ) is $1.96\sqrt{\frac{\hat{\phi }\left(1-\hat{\phi }\right)}{n}}$

For this reason, in order to get an accurate estimate of the overall outcome probability in the target population, based on the expected outcome proportion ($\hat{\phi }$) and the desired margin of error, the required sample size is calculated as: $n={\left(\frac{1.96}{\delta }\right)}^{2}\hat{\phi }\left(1-\hat{\phi }\right)$.

In general, we advise aiming for a margin of error of <0.05. Then assuming an anticipated outcome proportion in the study population of 0.4, then a minimum of 369 participants is needed to aim for an estimation error of no more than 0.05 around the actual value of 0.4 (51).

The study will include all adolescents with PCOS who attend the gynecology clinic of the Affiliated Hospital of Zunyi Medical University between January 2022 and December 2022, with an estimated sample size of 800. This study will recruit 400 healthy adolescent girls as the control group.

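### The study is sized for a binary outcome and promises absolute risks, but the plan builds a linear model, names no logistic model and leaves the form of the outcome open

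*Protocol article*

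**What the plan says.** Only the protocol article is at hand.

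- **Sample size and calculation** works from a yes/no outcome: "In the case of a binary outcome, an approximate 95% confidence interval for the total outcome proportion", "assuming an anticipated outcome proportion in the study population of 0.4".
- **Dependent variables** gives a CDI cut-off of 19 and a K-SADS-E interview diagnosis. It also allows either the CDI total or a threshold to be used, and does not say which is modelled.
- **Model-building procedures** describes a LASSO in glmnet with alpha equal to one.
- **Internal validation and assessment of model performance** tunes it by 10-fold cross-validation: "the lambda when it is one standard error away from the mean square error will be considered optimal". The next step is "After screening the variables, a multivariate linear model will be constructed". Performance is then judged by a C-statistic, a calibration plot of absolute risk and a scatter plot of fit. The same section describes variables with non-zero coefficients as significantly associated with depression.
- **External validation** plans a nomogram, and the abstract's discussion presents the absolute risk of depression as the product.

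Logistic regression, a logit link and a binomial family are not mentioned anywhere.

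**The concern.** The design and the promised outputs belong to a binary outcome. The fitting steps (mean square error, a linear final model, a scatter plot) are those one would write for a continuous outcome. An analyst who follows the text literally has two options, and neither gives what is promised:

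- **Model the 0/1 outcome linearly.** Nothing then keeps the predicted risks between 0 and 1, and a straight line misses the flattening of true risk near its limits.
- **Model the CDI total linearly.** The model is coherent, but it predicts a score. A calibration plot of absolute risk and a nomogram of risk do not follow from it.

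The final model is the study's product and is meant for use with individual girls, so its form should not be left to interpretation.

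A secondary matter is the order of steps, which is to screen variables first and then construct a model. This reads most naturally as a refit without a penalty. Such a refit on selected variables tends to give risks that are too extreme.

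**Working it through.** **1. The plan's own figure.** n = (1.96/δ)² × φ(1 − φ), with φ = 0.4 and δ = 0.05 ("we advise aiming for a margin of error of <0.05"):

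(1.96/0.05)² × 0.4 × 0.6 = 368.79, rounded up to 369.

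This matches "a minimum of 369 participants is needed". The number is right, and it comes from a binary-outcome formula.

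**2. Size of the problem on a 0/1 outcome.** This was checked by simulation.

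Inputs from the plan:
- Prevalence 0.4.
- A PCOS sample "with an estimated sample size of 800" over 12 months, of which January to August is for development, split 80/20. With even accrual, 800 × 8/12 × 0.8 ≈ 426 training patients.

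Inputs assumed, because the documents do not give them:
- Eight independent normal predictors, already selected, with equal effects.
- True risk logistic: logit(p) = b0 + Σ b·x, with b = SD/√8 and b0 set to give the prevalence.
- SD of the linear predictor varied from 0.7 to 2.0.
- Prevalence 0.2 as a sensitivity case.
- 200 replicates, each tested on 20,000 new subjects. Linear predictions were not truncated.

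Error is mean predicted minus mean true risk within the lowest tenth of predictions.

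| Prevalence | SD | C | Linear: outside 0–1 | Lowest tenth, linear | Lowest tenth, logistic | Mean absolute error, linear / logistic |
|---|---|---|---|---|---|---|
| 0.4 | 0.7 | 0.67 | 0.9% | −0.063 | −0.031 | 0.055 / 0.055 |
| 0.4 | 1.0 | 0.73 | 3.0% | −0.075 | −0.018 | 0.055 / 0.051 |
| 0.4 | 1.5 | 0.81 | 7.6% | −0.108 | −0.008 | 0.066 / 0.048 |
| 0.4 | 2.0 | 0.86 | 11.3% | −0.145 | −0.004 | 0.082 / 0.046 |
| 0.2 | 0.7 | 0.66 | 4.4% | −0.075 | −0.020 | 0.049 / 0.045 |
| 0.2 | 2.0 | 0.86 | 17.5% | −0.180 | −0.001 | 0.095 / 0.038 |

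The external cohort would be about 800 × 4/12 ≈ 267 patients. At prevalence 0.4, the range 0.9% to 11.3% is then roughly 2 to 30 girls with an impossible risk.

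At prevalence 0.4 the damage is at the low end. In the top tenth the linear model's error is only +0.031 to −0.007, no worse than logistic (+0.048 to +0.012). At prevalence 0.2 the top tenth suffers too, with error reaching −0.163 at SD 2.0.

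The C-statistics of the two models differ by at most 0.001 in every setting, so the planned discrimination measure is blind to the fault.

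**3. The refit, taken separately.** With the logistic link correct and no penalty, the calibration slope in new patients (ideal 1) was 0.84, 0.90, 0.93 and 0.92 at prevalence 0.4 for SD 0.7, 1.0, 1.5 and 2.0. At prevalence 0.2 it was 0.79 to 0.91. These runs omit the selection step. A separate simulation of selection followed by refit, at one setting (427 training patients, 45 candidate terms, attainable C 0.74), gave 0.72. The last two of those inputs are assumptions tried at a single value, so that figure shows direction only.

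**The case against.** Several stronger readings are tempting, and the document does not support them.

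- **That the outcome is settled as binary and the linear model is simply wrong for it.** The section on dependent variables leaves the CDI total available. On that reading mean square error, a linear model and a scatter plot fit together, and the absolute-risk output is what fails. The fault is that the sections do not agree.
- **That mean square error is itself an error.** Under a binomial model it is the Brier score, a proper loss. It is a problem only in company with a linear model.
- **That an unpenalised refit is specified.** The text says only that a model follows screening. The refit is an inference, although the natural one.
- **That a refit contradicts the plan's own reason for LASSO.** The Introduction's remark on overfitting ("pick more relevant independent variables to prevent overfitting") is about setting minor coefficients to zero and selecting variables. A refit on the selected variables keeps that.
- **That the plan cannot deliver risks, or that its calibration plot is invalid.** Most linear predictions stay within 0–1. At prevalence 0.4 and C of about 0.67 the average error equals that of logistic regression. A calibration plot remains a legitimate check and could expose the misfit in the tails.

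Two further points are fair. An article need not print every glmnet argument, so silence on the family is no finding by itself. And linear may be loose wording for a generalised linear model. Neither removes the difficulty: the article states a linear final model alongside absolute risks, and nothing in it says that logistic was meant.

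**Conclusion.** The point stands as an inconsistency that must be reconciled. The stated final model does not match the outcome used for the sample size or the absolute risks promised, and the form of the outcome is not fixed. This rests on the text alone.

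The size rests on the simulation's assumptions, including a truly logistic risk, which favours the logistic model. Under them, about 1% to 11% of patients receive impossible risks at the plan's own prevalence of 0.4, and about 4% to 18% at 0.2. Miscalibration at the extremes grows with discrimination and with lower prevalence. With weak discrimination at prevalence 0.4, the practical loss is small.

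The shrinkage point is secondary and conditional on an unpenalised refit. Calling non-zero LASSO coefficients significantly associated is a smaller wording fault, because selection is not a significance test.

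**What to change.** 1. Name one binary outcome for the model, either the CDI cut-off or the K-SADS-E diagnosis, and use it consistently in the sections on dependent variables, sample size and modelling.
2. State that the LASSO is logistic (glmnet with the binomial family) and that lambda is chosen by 10-fold cross-validated deviance or Brier score.
3. Replace the linear final model with a logistic one.
4. Say how the final coefficients are obtained. Either keep the penalised logistic coefficients, or refit the selected variables, multiply the coefficients by a bootstrap calibration slope and re-estimate the intercept. Both are defensible. Report calibration intercept and slope with the plot.
5. Describe variables with non-zero coefficients as selected.

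The cost is a few lines of text and a change of function arguments, plus bootstrap computing if the refit is kept. No new data are needed.

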**Methods and analysis:**

Model development and validation will be conducted using a retrospective study. The study will involve normal adolescent girls as the control group and adolescent PCOS patients as the experimental group. We will collect not only general factors such as individual susceptibility factors, biological factors, and psychosocial environmental factors of depression in adolescence, but will also examine the pathological factors, illness perception factors, diagnosis and treatment factors, and symptom-related factors of PCOS, as well as the outcome of depression. LASSO will be used to fit a multivariate warning model of depression risk. Data collected between January 2022 and August 2022 will be used to develop and validate the model internally, and data collected between September 2022 and December 2022 will be used for external validation. We will use the C-statistic to measure the model's discrimination, the calibration plot to measure the model's risk prediction ability for depression, and the nomogram to visualize the model.

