
## Objectives

The aims of the study are to: (i) Develop a depression prediction model for adolescents with PCOS to identify at-risk populations early; (ii) Validate the accuracy and validity of the model and to assess the clinical utility of the model.

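### The calibration plot is the only stated measure of absolute-risk accuracy; a calibration intercept and slope with 95% CIs, from the development model's fixed coefficients, should be added

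*Protocol article*

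**What the plan says.** Objective (ii) is to "Validate the accuracy and validity of the model". The section on internal validation and assessment of model performance divides prediction accuracy into two parts and gives each a tool. For ranking, "the C-statistic is used to measure discrimination". For the size of the risks, the tool is the plot, "followed by a calibration plot to measure the accuracy of the absolute risk predictions of the warning model". One further check is listed: "An evaluation of the fit will be performed by drawing a scatter plot". The abstract makes the same assignment: "the calibration plot to measure the model's risk prediction ability for depression".

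The article gives no calibration intercept, slope, other numerical calibration summary, confidence band or criterion. The sample-size section addresses only the overall proportion with depression. The external validation section names no calibration measure of its own and says that the model is to be refitted in the September-December cohort.

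**The concern.** The abstract presents the absolute risk of depression as the product of the study, and the model is to reach clinicians as a nomogram. The C-statistic depends only on ranking, so it cannot show that predicted risks are too extreme. That fault is plausible here: LASSO screens roughly 30 candidate predictors, several of them split into categories, and a further model is then built on the selected variables with no penalty stated.

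Detecting the fault is therefore left to a graph. A graph does not say by how much the risks are too extreme or how precisely this is known, and it gives two readers no common basis for a conclusion. If the reading is wrong, the answer to objective (ii) is wrong for the quantity clinicians would use.

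**Working it through.** **1. The plan's own figure.** With a proportion of 0.4 and a margin of 0.05, n = (1.96/0.05)² × 0.4 × 0.6 = 368.8, rounded up to 369. This reproduces the statement that "a minimum of 369 participants is needed to aim for an estimation error of no more than 0.05". It concerns the overall proportion and says nothing about calibration.

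**2. Size of the validation sets.** The article expects 800 girls with PCOS over 12 months and an 80/20 split of January-August.
- Even accrual: 800 × 8/12 = 533 for development, of which 20% = 107. September-December: 800 × 4/12 = 267.
- At the 80-100 patients per month given under Participants: 20% of 640-800 = 128-160, and four months give 320-400.
- If the 400 controls are included and split the same way (an assumption): 160 and 400.

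**3. Noise per plotted group.** The 95% half-width at an observed risk of 0.4 is 1.96 × √(0.4 × 0.6 / k), with k girls per group.

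| Set | Groups | k | Half-width |
|---|---|---|---|
| n = 107 | 5 | 21.4 | 0.21 |
| n = 107 | 10 | 10.7 | 0.29 |
| n = 267 | 5 | 53.4 | 0.13 |
| n = 267 | 10 | 26.7 | 0.19 |
| n = 400 | 10 | 40 | 0.15 |

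**4. What a slope would add.** Fit logit P(depression) = a + b × LP, where LP is the linear predictor from the development model. Perfect calibration has b = 1; overfitting has b < 1. The inputs below are assumptions, because the article gives none: 40% events (its own planning value), a normal linear predictor, and correct mean risk.

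*First simulation*, 1,000 replicates per setting, true linear-predictor SD 0.75 to 1.3 (C-statistic about 0.69 to 0.79). Ranges are over these SDs.

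| True slope | n | Slope CI excludes 1 | Every group's 95% interval covers its mean predicted risk |
|---|---|---|---|
| 0.6 | 107 | 52-75% | 22-38% |
| 0.6 | 267 | 88-98% | 2-10% |
| 0.7 | 107 | 28-46% | 41-60% |
| 0.7 | 267 | 56-77% | 15-31% |
| 0.7 | 400 | 71-91% | 7-19% |
| 0.8 | 107 | 13-22% | 62-72% |
| 0.8 | 267 | 26-41% | 32-45% |
| 1.0 | 107 | 5-6% | 78-80% |
| 1.0 | 267 | 4-5% | 62-65% |

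Five groups were used at n = 107 and ten otherwise. The last two rows show that this strict reading of the plot also faults 35-38% of perfectly calibrated models at n = 267. At true slope 0.7 the slope's mean standard error is 0.17-0.23 (n = 107), 0.10-0.14 (n = 267) and 0.08-0.11 (n = 400).

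*Second simulation*, n = 267, SD 1.2 on the predicted scale, ten groups, three ways of judging. The pattern reading counts a plot as showing overfitting if the bottom three deciles lie on average more than 0.03 above the line and the top three more than 0.03 below it.

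| True slope | Slope CI excludes 1 | At most one bin off the line | Pattern reading flags overfitting |
|---|---|---|---|
| 0.6 | 87% | 40% | 79% |
| 0.7 | 60% | 62% | 55% |
| 1.0 | 4% | 92% | 6% |

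With the SD of 1.2 placed on the true scale instead, the slope CI excludes 1 in 97% (slope 0.6) and 76% (slope 0.7).

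**5. Reading the results.** The verdict from the plot changes with the rule. At n = 267 and true slope 0.6, the model escapes in 40% of samples under the one-bin rule, but in only 21% (100 − 79) under the pattern reading. The slope needs no such rule and comes with its own uncertainty.

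**The case against.** The strongest reply is that a calibration plot is a standard tool, that the article commits to expert guidance and TRIPOD reporting, and that accompanying statistics and the drawing of the plot are details an article leaves to a fuller document. Part of this stands. Naming a plot is not an error, the article does not exclude further statistics, and it specifies neither deciles nor the absence of a smoother or band. But it says twice what the measure of absolute-risk accuracy is, and that measure yields no estimate. Improving a stated choice differs from asking for detail left elsewhere.

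A reader might infer that a clearly overfitted model would often pass in both validation sets. The documents do not support that. The article states no rule for reading the plot, and the one-bin rule behind the 40% figure is an assumption. A reader looking for low-risk groups above the line and high-risk groups below it would usually see a slope near 0.6 at n = 267 or more. The external cohort may also be 320-400 rather than 267.

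Two more objections stand. In the 20% set the slope is weak as well: at true slope 0.7 its CI still includes 1 in 54-72% of replicates, so sample size is the limit there. And a slope computed after refitting in the external cohort would look good by construction, so the recommendation only works with fixed coefficients.

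**Conclusion.** The point holds as a cheap improvement to a stated method. The plan's only named measure of absolute-risk accuracy provides neither an estimate nor its uncertainty, and at the expected cohort sizes moderate overfitting (slope about 0.7 to 0.8) can be missed or judged inconsistently. The gain from a slope is modest: at n = 267 and true slope 0.7, detection is about 60-75%, against about 55-60% for a simple pattern reading. At slope 0.8 the CI excludes 1 in only 26-41% of samples at that size, so the benefit there is mainly an estimate with honest uncertainty. In the 20% set neither approach is precise.

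These sizes rest on an assumed spread of the linear predictor, assumed slopes, grouping and reading rules, even accrual and 40% events. That the plot yields no estimate does not depend on them. There is no ground for calling the plot wrong or for asking that the scatter plot be dropped.

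**What to change.** In the section on internal validation and assessment of model performance, and again under external validation, state the following:
- Calibration-in-the-large (logistic model with the linear predictor as an offset) and the calibration slope will be reported with 95% CIs in the 20% set and in the September-December cohort.
- Both will be computed from the development model's fixed coefficients. Any refitted model will be reported separately and not used to judge calibration.
- The calibration plot will be drawn as a smoothed curve with a confidence band.
- The conclusion on calibration will rest on the intercept and slope, with the plot as the display. The text will say that the slope from the 20% set is imprecise.

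The scatter plot may stay. The cost is a few sentences and one or two simple logistic fits per cohort, with no new data. The reported performance may look less favourable.
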